### Randomization

In stage 1, the sample will be divided into two groups of 40 participants each—experimental group and control group. The allocation and the randomization will be performed by a blinded researcher. The assignment of subjects to each group will be made through a system of sealed envelopes. Subsequently, for the pilot study in stage 2, we will create a group that will receive the app reminders on their mobile phones—the mobile phone group—and another group that will not receive the app reminder—the no mobile phone group. Group allocation will depend on whether the participant has a mobile phone and if its characteristics are adapted to the requirements of the study.

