The evaluation of the variables and the execution of the advised tasks will be carried out at participants’ homes 2 and 4 weeks following the initial assessment. Researchers will analyze and compare the data obtained from the outcome variables of the experimental group and the control group to check whether the educational intervention was effective in patients who have suffered stroke and who have been discharged to their homes. If the hypothesis is confirmed, the educational intervention would be implemented in the control group.

#### Stage 2

For the pilot study in stage 2, one group will receive the app reminders on their mobile phones—mobile phone group—and another group will not—no mobile phone group. Placement in the first group depends on whether the participant has a mobile phone and if its characteristics are adapted to the requirements of the study. The app will provide the advice previously given by the therapist in the participants’ homes. The timing of reminders will differ for each participant depending on the amount of advice given. However, in the 4 weeks of the app being used, each piece of advice will be given three times. The mobile phone will beep once for each piece of advice and the participant must check and mark the option indicating whether he has or has not complied with the advice. After this period, the outcome variables will be analyzed in both groups to check whether there are differences between the two groups.

After 8 weeks, and after having removed the app from mobile phones of the mobile phone group, we will reanalyze the outcome variables. Will do this by testing both groups to see whether the mobile phone group participants have continued to perform the advised tasks provided by the therapist, and if differences still exist between them and the no mobile phone group. If so, a reminder system will be implemented in the no mobile phone group. Figure 2 shows the outline of the entire study protocol, including steps in stage 1 and stage 2.

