### Statistical Analyses

Descriptive analyses will include mean, standard deviation, and 95% confidence intervals of the values for each variable. The normality of the variables will be performed using the Kolmogov-Smirnov (KS) test. Preintervention values prior to each condition will be compared. A 2x2 mixed-model analysis of variance (ANOVA) with supplementation (mobile phone group or no mobile phone group) as the between-subjects variable, and time (pre- and postintervention) as the within-subjects variable will be used. Intergroup effect sizes will be calculated (Cohen’s d). An effect size <0.2 reflects a negligible difference, between ≥0.5 and ≤0.8 a moderate difference, and ≥0.8 a large difference. A *P* value <.05 will be considered statistically significant. Data will be analyzed using SPSS version 19.0.

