## Discussion

### Implications of the Study

The aim of this study is that patients who suffer stroke and who have been discharged to their homes improve the performance of ADL in the home environment, in spite of the restrictions caused by the stroke, after advice given by the therapist. A secondary aim is that these patients continue the treatment through a reminder app installed on their mobile phones (isoTimer).

Some studies have analyzed the ergonomics of the workplace through a tool and other studies have carried out different kinds of treatments at home on people with stroke. Because of this, it is thought that an educational intervention at home with people who have suffered a stroke and who have been discharged to their homes could be an innovative and necessary study.

The use of a mobile phone reminder app is an innovative method because the mobile phone has been used with people who have suffered a stroke, but it has not been used before as a means of improving adherence to treatment at home with this population. This method could result in advances in facilitating the continuity of treatment in this population once they return to their homes.

This study could be a breakthrough in the treatment of people who have suffered a stroke and who have been discharged to their homes, since during the first months the largest changes occur and it is essential to continue the rehabilitation treatment received at the hospital. The HTAS tool would allow a proper assessment of the home environment and the implementation of the ADL by the patient, bringing some useful advice that will guide them through the process of recovery of functional independence. Also, being able to have an app that reminds them of the advice provided by the therapist ensures that all patients who suffer a stroke and are discharged to their homes do not encounter barriers in the environment, and that they can advance their functional independence. Additionally, this continuity in the treatment without interruption and its early implementation would favor not only the recovery and rehabilitation of the patient, but could also result in cost savings in care services.

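### The only inferential model is a pre/post ANOVA of the non-randomised phone groups, so the randomised stage 1 comparison has no fitting model and no deciding visit

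*Protocol article*

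**What the plan says.** **Model.** Statistical Analyses specifies a mixed ANOVA of 2x2 form. The section describes the time factor thus: "time (pre- and postintervention) as the within-subjects variable will be used". For the group factor it names the stage 2 groups: "supplementation (mobile phone group or no mobile phone group) as the between-subjects variable". Baseline values are to be compared between conditions. No other inferential model appears in the article.

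**Stage 1.** Under Randomization, 80 participants are split into experimental and control groups of 40. Under Procedure, outcomes are measured at the initial assessment and again "2 and 4 weeks following the initial assessment". The two arms are then compared to judge whether the intervention worked, and "If the hypothesis is confirmed, the educational intervention would be implemented in the control group".

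**Stage 2.** This is a pilot within the experimental group. Under Randomization, "Group allocation will depend on whether the participant has a mobile phone" and on whether that phone is suitable. Outcomes are analysed after the app period and once more later: "After 8 weeks, and after having removed the app from mobile phones of the mobile phone group, we will reanalyze the outcome variables".

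**Primary variable.** Table 1 marks the Barthel Index as the main variable. The sample size section uses a difference on the Functional Independence Measure (FIM), with d=0.59 and 40 per group.

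**The concern.** The model and the trial's main question do not meet. The randomised contrast is experimental against control, and the only model given has a different group factor. If the 2x2 layout is meant for stage 1 as well, its two time levels cannot hold three visits: either one follow-up is dropped, or the post value may be week 2 or week 4 at the analyst's choice.

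That choice matters because the stage 1 result triggers a further step, treatment of the control group. A decision of that kind needs one test fixed beforehand. If two visits are available and neither is named, a favourable result at either can be read as confirmation.

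A smaller matter is efficiency. In a 2x2 pre/post ANOVA the group-by-time test is a t test on change scores. Baseline is collected anyway, and using it as a covariate is at least as precise in a randomised comparison, apart from the loss of one degree of freedom.

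**Working it through.** **1. Model against visits**

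| | Groups | How formed | Outcome occasions |
|---|---|---|---|
| Stated ANOVA | phone / no phone | phone ownership and suitability | 2 (pre, post) |
| Stage 1 | experimental / control | randomised | 3 (baseline, week 2, week 4) |
| Stage 2 | phone / no phone | phone ownership and suitability | 3 (before app, end of app, 8-week re-analysis) |

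The stated model matches stage 1 neither in its groups nor in its occasions. It matches stage 2 in groups, though there too one time factor with two levels covers only one of the two later analyses.

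**2. Type I error if either visit counts**

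Two tests, each two-sided at 0.05, with correlation c between the test statistics. The documents do not give c; 0.5 to 0.9 is assumed. The chance of at least one false positive is 1 − P(|Z1| < 1.96 and |Z2| < 1.96), with Z1 and Z2 bivariate normal.

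- c = 0.9: about 7%
- c = 0.5: about 9%
- independent tests, as an upper reference: 1 − 0.95² = 9.75%

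**3. The plan's own sample size figure**

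The inputs are d=0.59, alpha 0.05 (sidedness not stated) and beta 0.08, from Sample Size Calculation. A two-sample t test with 40 per group has 74.1% power two-sided and 83.4% one-sided. Power of 92% would need 67 per group two-sided or 55 one-sided. So the printed 40 does not reproduce. That is a separate matter; here d=0.59 and 40 per group serve only as a common basis for comparing methods.

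**4. Change score against ANCOVA, if the 2x2 form were used for stage 1**

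Let rho be the correlation between baseline and follow-up (not in the documents, assumed) and let the follow-up SD be 1. With equal SDs:

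- change-score variance: 2(1 − rho), so the effective d is 0.59/√(2(1 − rho))
- ANCOVA variance: 1 − rho², so the effective d is 0.59/√(1 − rho²)
- ratio of ANCOVA to change-score variance: (1 + rho)/2, below 1 for every rho below 1

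Power comes from the noncentral t distribution, two-sided 0.05, with 78 degrees of freedom for the change score and 77 for ANCOVA.

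| rho | Effective d, change | Effective d, ANCOVA | Power, change | Power, ANCOVA |
|---|---|---|---|---|
| 0.3 | 0.59/√1.40 = 0.499 | 0.59/√0.91 = 0.618 | 59.6% | 78.0% |
| 0.5 | 0.59/√1.00 = 0.590 | 0.59/√0.75 = 0.681 | 74.1% | 85.3% |
| 0.7 | 0.59/√0.60 = 0.762 | 0.59/√0.51 = 0.826 | 92.0% | 95.4% |
| 0.8 | 0.59/√0.40 = 0.933 | 0.59/√0.36 = 0.983 | 98.5% | 99.1% |

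**5. Unequal SDs**

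If the baseline SD is k times the follow-up SD, the change-score variance is 1 + k² − 2·rho·k, and the ANCOVA variance stays at 1 − rho². Take k = 0.6 as an assumption.

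- rho = 0.3: 1 + 0.36 − 0.36 = 1.00 against 0.91; power 74% against 78%
- rho = 0.5: 1 + 0.36 − 0.60 = 0.76 against 0.75; power 85% for both

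The gain shrinks to about 0 to 4 points.

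**The case against.** **The ANOVA was never offered as the stage 1 model.** This is correct. The sentence names the phone groups, so it is wrong to say that the plan analyses the randomised arms by a two-level model and thereby loses power. The power figures above describe a use that the text does not state. But this does not rescue the plan: read literally, the randomised comparison has no model at all.

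**A journal article may leave detail to a fuller document.** Covariates, a repeated-measures model and missed visits can fairly be left there, and the study flowchart is not visible to this review. What stands is what the article itself fixes: a single model attached to the pilot contrast, and a decision attached to a result without a visit.

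**Change-score analysis is valid under randomisation.** It is. The issue is efficiency, not bias, and its size depends on a correlation and an SD ratio that the documents do not give.

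Three stronger readings are tempting and are not supported:

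- A reader might infer that the Barthel entry range of 0 to 49 narrows baseline, lowers rho and so penalises change scores most. The reverse holds. Selection on baseline in a linear model leaves slope and residual variance unchanged. With slope 0.5 and only the lower half of a normal baseline kept, rho falls from 0.50 to 0.33, but the ANCOVA-to-change variance ratio rises from 0.75 to 0.89.
- A reader might carry the ANCOVA advantage over to stage 2. Those groups are not randomised, so the two methods can estimate different effects there, and ANCOVA is not simply the more powerful version.
- A reader might infer, from the remark that "during the first months the largest changes occur", that time since discharge must be a covariate. The remark makes it a reasonable option, not a requirement.

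**Conclusion.** The point holds as one of missing fit and a missing decision rule. The randomised stage 1 comparison has no matching model and no named visit, while its result triggers a further step. This rests on the text alone.

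The cost in type I error, about 7% to 9% in place of 5%, assumes that significance at either visit would count. The plan does not say that it would; it leaves this open.

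The efficiency argument is secondary and conditional on the 2x2 form being used for stage 1. With equal SDs, ANCOVA adds 18 points of power at rho 0.3 (78.0 − 59.6), 11 at 0.5 and 3 at 0.7, and less than 1 at 0.8. With a baseline SD of 0.6 of the follow-up SD, it adds about 0 to 4 points. The effect size d=0.59 was set on the FIM, so applying it to the Barthel Index is a further assumption.

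**What to change.** State the stage 1 primary analysis separately: an ANCOVA of the 4-week Barthel Index on randomised arm, adjusted for baseline Barthel Index, two-sided at 0.05. Week 4 is the last stage 1 visit, and the Barthel Index is already the main variable. Say that this test alone determines whether the stage 1 hypothesis counts as confirmed. Report week 2 as secondary. Time since discharge may be added as a covariate if it is named in advance.

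Keep the phone-group ANOVA for stage 2, labelled exploratory and non-randomised, and say which stage 2 occasion is the post value. The article gives the app period as 18 weeks under Educational Intervention but 4 weeks under Procedure ("in the 4 weeks of the app being used, each piece of advice will be given three times"). These passages must be reconciled before that occasion can be defined.

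The cost is analysis wording only. The measurements are already planned, no participant or visit is added, and the named software can fit the model.

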### Sample Size Calculation

A power analysis was conducted using the program G*Power 3.1. A priori, a sample of approximately 40 participants per group for the stage 1 intervention is needed to detect a significant difference (17.3 in the FIM [39]) between the experimental group and the control group (effect size d=0.59, alpha=.05, beta=.08). The randomization will be performed by a blinded researcher.

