### Outcome Measure

The outcome measure of this study will allow us to know and assess the level of patient dependency, cognitive ability, quality of life, social support, and physical condition. All of these factors will be measured by the Barthel Index, the Functional Independence Measure, the Mini-Mental State Examination, the Canadian Neurological Scale, the Stroke Impact Scale-16, the Trunk Control Test, the Modified Rankin Scale, the Multidimensional Scale of Perceived Social Support, the Quality of Life Scale for Stroke, the Functional Reach Test, the Romberg Test, the Time Up and Go test, the Timed-Stands Test, a portable dynamometer, and a sociodemographic questionnaire (see Table 1).

In addition, visits to the emergency department, the general practitioner, and specialists after discharge from hospital to home, as well as taking drugs associated with stroke, will be controlled.

**Table 1 table1:** Outcome measures of the study.

Test or scale (acronym), reference	Measure	Items, n	Statistical treatment, reference	Variable type
Barthel Index (BI) [39-41]	Level of dependence	10	κw=.93 (95% CI 0.90-0.96) random effects modeling [42,43]	Main
Functional Independence Measure (FIM) [39]	Level of dependence	18	ICC^a^=.124-.661 [44]	Secondary
Mini-Mental State Examination (MMSE) [38]	Cognitive disability	11	ICC=.69 [45]	Secondary
Canadian Neurological Scale (CNS) [46]	Cognitive and motor function	7	κ= 0.76 [47]	Secondary
Stroke Impact Scale-16 (SIS-16) [48]	Quality of life	16	ICC=.70-.92 [49]	Secondary
Trunk Control Test (TCT) [50]	Trunk control	4	ρ=.76, *P*<0.001 [51]	Secondary
Modified Rankin Scale (MRS) [52]	Functional independence	1	Rater 1: κ=.81, .94 and Rater 2: κ=.95, .99 [53]	Secondary
Perceived Social Support Scale (MSPSS) [54,55]	Social support	12	ρ=.72-.85 [54]	Secondary
Quality of Life Scale for Stroke (ECVI-38) [56]	Quality of life	38	ICC=.81-.96 [56]	Secondary
Functional Reach Test (FRT) [57]	Stability	NA^b^	ICC=.90-.95 [58]	Secondary
Romberg Test (RT) [59]	Balance	NA	ICC=.84-.97 [60,61]	Secondary
Time Up and Go (TUG) [62]	Balance, mobility, and fall risk	NA	ICC=.96 [58]	Secondary
Portable dynamometer [63]	Strength in the upper limbs	NA	ICC=.98 [60]	Secondary
Timed-Stands Test (TST) [64]	Strength in the lower limbs	NA	ICC=.994 [65]	Secondary
Sociodemographic questionnaire	Sociodemographic data	25	NA	Secondary

^a^interclass correlation (ICC).

^b^not applicable (NA).

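### The sample size is justified on the FIM, a secondary outcome; no power is given for the Barthel Index, the only outcome labelled main

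*Protocol article*

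**What the plan says.** The Sample Size Calculation section of the protocol article holds the only power statement. It says that "a sample of approximately 40 participants per group for the stage 1 intervention is needed" and gives the purpose as "to detect a significant difference (17.3 in the FIM [39]) between the experimental group and the control group". The parameters are "effect size d=0.59, alpha=.05, beta=.08". The Randomization section carries the number forward: "the sample will be divided into two groups of 40 participants each".

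Table 1, under Outcome Measure, assigns each measure a variable type. The Barthel Index row reads "Barthel Index (BI) [39-41] Level of dependence 10 κw=.93 (95% CI 0.90-0.96) random effects modeling [42,43] Main" and the FIM row reads "Functional Independence Measure (FIM) [39] Level of dependence 18 ICC^a^=.124-.661 [44] Secondary". The Barthel Index is the only entry typed as main; all the others are secondary.

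**The concern.** A sample-size statement should tell the reader how likely the trial is to detect a stated difference on its main outcome. Here the stated difference, effect size and power belong to a different scale, which the same article ranks as secondary. No Barthel difference, standard deviation, effect size or power appears anywhere in the article.

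This is a conflict between two things that the article does state, its main outcome and its power basis. It is not a detail that an article would normally leave to a fuller document. At stake is how the stage 1 result is read. If the Barthel comparison is not significant, the document gives no basis for judging whether the trial could have found a difference worth having, and the 92% implied by beta .08 could wrongly be taken as that basis.

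**Working it through.** **Inputs from the document.** FIM difference 17.3; d=0.59; alpha .05, sidedness not stated; beta .08, so power 1 − 0.08 = 92%; 40 per group, 1:1 (Sample Size Calculation; Randomization). The Barthel Index is main and the FIM secondary (Table 1).

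**Inputs not in the document.** There is no Barthel difference or standard deviation. The values 15, 20 and 25 used below are assumptions for illustration.

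**Step 1: the plan's own figure.** For two independent means, n per group = 2(z_alpha + z_beta)² / d², with d² = 0.59² = 0.3481.

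- Two-sided, 92% power: 2(1.960 + 1.405)² / 0.3481 ≈ 65.1, so 66 (t test 66.03, so 67).
- One-sided, 92% power: 2(1.645 + 1.405)² / 0.3481 ≈ 53.4, so 54 (t test 54.13, so 55).
- Two-sided, 80% power: 2(1.960 + 0.842)² / 0.3481 ≈ 45.1, so 46 (t test 46.08, so 47).
- One-sided, 80% power: 2(1.645 + 0.842)² / 0.3481 ≈ 35.5, so 36 (t test 36.22, so 37).

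None of these gives 40. A change-score analysis would give 40 at 92% power with an assumed pre-post correlation of about 0.7, but the document states no such correlation. That the FIM figure does not reproduce is a separate matter. It matters here only because the 92% cannot be borrowed for the Barthel Index.

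**Step 2: power if d=0.59 applied unchanged to the Barthel Index.** Normal approximation: 0.59 × √(40/2) = 2.639.

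- Two-sided: Φ(2.639 − 1.960) = 75% (t test 74%).
- One-sided: Φ(2.639 − 1.645) = 84% (t test 83%).

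**Step 3: what 40 per group can detect** (two-sided .05, t test). The smallest detectable d is 0.634 at 80% power and 0.762 at 92%. Multiplying by the assumed standard deviation gives Barthel points:

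| Assumed Barthel SD | 80% power (d=0.634) | 92% power (d=0.762) |
|---|---|---|
| 15 | 9.5 | 11.4 |
| 20 | 12.7 | 15.2 |
| 25 | 15.9 | 19.0 |

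**Step 4: sensitivity to the unknown Barthel effect.** With 40 per group (two-sided .05, t test), power is 42% at d=0.4, 60% at d=0.5, 74% at d=0.59, 87% at d=0.7 and 94% at d=0.8. The answer depends on an input that the document does not give.

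**The case against.** The strongest defence is that both scales carry the same construct label in Table 1, level of dependence, and share reference 39, which is also the source cited for the 17.3. Borrowing an effect from a closely related scale is a recognisable choice, and an article may condense a fuller justification. This softens the point but does not remove it. The sample-size paragraph names the FIM explicitly, so 17.3 cannot be read as a Barthel figure, and no sentence carries the effect across. A standardised effect depends on the spread and responsiveness of the scale in the enrolled patients, so it does not transfer by shared construct alone.

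Three stronger readings are tempting, and the document supports none of them.

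- A reader might infer that it is open which scale decides the trial. Table 1 types exactly one variable as main, so the hierarchy is fixed in print. What is missing is the power for that outcome.
- A reader might infer that d=0.59 overstates the Barthel effect because entry is limited to Barthel scores of 0 to 49. The limit applies at baseline only, follow-up scores can exceed it, and a narrower spread would raise d for a given point difference. The document does not settle the direction.
- A reader might infer that the trial is shown to be underpowered on the Barthel Index. With no Barthel difference or standard deviation stated, that cannot be shown. The point values above illustrate a range only.

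**Conclusion.** The point holds in this form: the only stated power concerns a secondary outcome, and the single main outcome has no stated target difference, standard deviation or power. The mismatch follows directly from the Sample Size Calculation section and Table 1 and needs no assumption.

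The size of the consequence does rest on assumptions: an unadjusted two-group t test with all 40 per group analysed and, for the values in points, the illustrative standard deviations. On that basis 40 per group detects d=0.63 at 80% power and d=0.76 at 92%, and d=0.59 would have about 74% power two-sided or 83% one-sided. An analysis that uses baseline values could do better, depending on a correlation that is not stated. The point should be addressed, but it does not invalidate the design.

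**What to change.** Keep the Barthel Index as the single main outcome. Rewrite the sample-size paragraph to state the power, or the detectable Barthel difference, that 40 per group gives, with the assumed Barthel standard deviation and its source, the sidedness of the test and the intended power. Keep the FIM calculation as supportive and label it so. If the FIM was in fact meant to be primary, correct Table 1 instead, before outcome data are examined.

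Either route is a change of text: one paragraph or the variable-type entries in one table. The enrolled number stays as planned, since the rewrite reports what that number delivers. The downside is that the stated power may become less favourable than the 92% now implied. Recruitment is already under way according to the Results section, so the change should be dated and made before analysis.

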### Participants

The total sample will consist of 80 adults who have suffered a stroke with moderate severity (score between 0 and 49 on the Barthel Index [37]), who have been discharged to their homes in the 3 months prior to recruitment to the study [28]. The sample will be taken from the Carlos Haya Hospital complex in Málaga, Spain.

Individuals with dementia or other severe cognitive impairment (scoring 0 to 17 in the Mini-Mental State Examination) will not be included [38].

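### 40 per group with d = 0.59 and alpha .05 gives about 74% power, not the 92% that beta = .08 implies

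*Protocol article*

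**What the plan says.** The Sample Size Calculation section of the protocol article states: "A power analysis was conducted using the program G*Power 3.1". It concludes that "a sample of approximately 40 participants per group for the stage 1 intervention is needed", and gives the target as the number "needed to detect a significant difference (17.3 in the FIM [39]) between the experimental group and the control group". The inputs follow in brackets: "effect size d=0.59, alpha=.05, beta=.08".

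The rest of the article fixes the same size. Under Participants: "The total sample will consist of 80 adults". Under Randomization: "the sample will be divided into two groups of 40 participants each".

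The sample size text states no sidedness, standard deviation, pre-post correlation or allowance for losses. The Statistical Analyses section plans a 2x2 mixed-model ANOVA and sets the criterion "A *P* value <.05 will be considered statistically significant".

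**The concern.** An effect size, an alpha, a beta and a group size are all printed, and any three of them determine the fourth for a given test. Here the four do not agree. A moderate effect of d = 0.59 with 40 per group is well short of what 92% power requires.

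The calculation is the only support for the sample size. As printed, it tells readers that the trial has an 8% chance of missing the target difference in stage 1. If the true figure is about 26%, a non-significant result says much less about the intervention than the protocol suggests. It also matters inside the trial, because the Procedure section makes offering the intervention to the control group conditional on the hypothesis being confirmed.

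**Working it through.** **Inputs, all from the Sample Size Calculation section unless noted**

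- Standardized difference d = 0.59 (17.3 FIM points, so an implied SD of 17.3/0.59 = 29.3)
- alpha = .05
- beta = .08, so power = 1 − .08 = .92
- n = 40 per group, 1:1 (also in Randomization)
- Sidedness is not stated. Two-sided is taken as the main case because the planned ANOVA F test is non-directional. One-sided is shown as well.

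**Step 1: power at the planned size.** For two independent groups, the noncentral t calculation (the one G*Power uses for d) has

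- noncentrality = d × √(n/2) = 0.59 × √20 = 2.64
- df = 2 × 40 − 2 = 78
- critical t = 1.991 two-sided, 1.665 one-sided

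This gives power of 0.741 two-sided (beta 0.26) and 0.834 one-sided (beta 0.17). The normal approximation gives 0.751 and 0.840. The plan's 0.92 is not reproduced.

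**Step 2: group size needed for d = 0.59.** Solving the same formula for n:

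| Target power | Two-sided, n per group | One-sided, n per group |
|---|---|---|
| 80% | 47 | 37 |
| 92% (beta = .08) | 67 | 55 |

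No cell is 40. At 92% power the shortfall is 67 − 40 = 27 per group two-sided, or 55 − 40 = 15 one-sided.

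**Step 3: effect detectable with 40 per group, two-sided.** 92% power needs d = 0.76. 80% power needs d of about 0.63 (0.634 to three decimals; exactly 0.63 gives 79.5%).

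**Step 4: does using the baseline rescue the figure?** In a 2x2 mixed ANOVA the group-by-time test is equivalent to a t test on change scores. If d is scaled on the raw-score SD and the pre-post correlation is ρ, the effective effect size is d/√(2(1 − ρ)). For baseline-adjusted ANCOVA it is d/√(1 − ρ²). With 40 per group, two-sided, and ρ assumed:

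| Assumed ρ | Change score | ANCOVA |
|---|---|---|
| 0.5 | 74% | 85% |
| 0.6 | 83% | 90% |
| 0.7 | 92% | 95% |

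At ρ = 0.70 the change-score effect size is 0.59/√0.6 = 0.762, which does give 92%. The article states no correlation.

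**Step 5: illustration of losses.** The article gives no loss rate, so this is an assumption. With 10% lost (36 per group), two-sided power on final scores is 69%. With 20% lost (32 per group) it is 64%.

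**The case against.** The strongest reply is that the 74% figure rests on choices the article does not state, and that other choices come closer.

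- **One-sided test.** The hypothesis is directional, so a one-sided entry in G*Power is possible. It raises power to 83%, which is still not 92%.
- **Misprinted beta.** If 80% power was intended with a one-sided test, 37 per group suffice, and an allowance of about 8% gives 37/0.92 = 40.2. This is plausible. It needs three things the text does not say: a misprint, a one-sided test and an allowance for losses. The printed beta would be wrong even so.
- **Repeated measures.** A change-score calculation with a correlation of 0.70 matches beta = .08 almost exactly. It cannot be ruled out. But the text presents d as a difference between the experimental and control groups and gives no correlation, and the ANOVA in the Statistical Analyses section names the stage 2 mobile phone groups as its between-subjects factor.
- **Losses.** A condensed article may leave an attrition allowance to the full protocol. This is fair: the missing allowance is not counted as an error here, and Step 5 is illustration only.

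What stands is a limit on certainty about the cause. It is not known which entry was wrong or left out. The printed numbers still do not agree under a two-group t test, one-sided or two-sided, and the word approximately cannot stretch 40 to 55 or 67.

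**Conclusion.** The stated power is wrong as written. On the printed inputs, 40 per group gives 74% power (two-sided t test on final scores, no losses) against the 92% implied, so the chance of missing the target effect is 26% and not 8%, more than three times as high. With a one-sided test the power is 83% and the type II error 17%. Only a further assumption that the article does not report, such as a pre-post correlation near 0.70 with a change-score analysis, brings the figure to 92%. The mismatch does not depend on the choice of sidedness; the exact size of the shortfall does.

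**What to change.** Correct the Sample Size Calculation sentence. State which G*Power test was run, one- or two-sided, with any correlation assumed and the intended beta, and then change whichever figure is wrong. If no further assumption lay behind the calculation, the statement should be that 40 per group gives 74% power for d = 0.59, or 80% power for d of about 0.63, at two-sided alpha .05 and before losses.

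If the stage 1 comparison is to be analysed by baseline-adjusted ANCOVA, the power may be stated on that basis with the assumed correlation beside it, for example 85% at a correlation of 0.5.

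The cost is one revised sentence and a less favourable power figure. No additional patients are needed for the correction.
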